**PACD**

The PACD will be used to evaluate daily asthma symptoms in children aged 1–5 years (54). The electronic diary includes various questions that have to be answered in the evening for daytime symptoms and the previous night. The combined daytime score is the average of scores from questions 4–7 in the diary which are questions regarding severity of cough, wheezing, trouble breathing, and interference with activities, scores for each question range from 0 (best) to 5 (worst). Using a symptom diary during 12 months will allow the symptom load of the patients and the asthma severity in treated vs. control patients to be defined and documented. It is preferred the same parent/guardian answers the questions during the study. The PACD questions will be collected electronically by the TIPPDiary app.

In order to reduce the burden of parents, the electronic diary should not be filled out daily all year round. It is well known from many studies that asthma exacerbations occur particularly in autumn, winter and spring. For this reason, no diary should be kept for 4 months in the months of May, June, July and August. If the patients are recruited in the summer months, they only need to keep an electronic diary between visit 1 and visit 2.

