## Determination of primary and secondary measures

**The primary efficacy endpoint** is the time to first severe exacerbations defined by hospitalization and/or at least 3 days of systemic steroids or one day of rectal prednisolone (Rectodelt®). Severe exacerbations were chosen as primary outcome because they are patient-important outcomes that have significant consequences for children, caregivers, and the health care system.

**Key secondary endpoint(s) for all patients:** Secondary endpoints for all patients:

- Number of severe exacerbations
- Exacerbation-free survival time defined as the time from randomization until the first severe exacerbation.
- Percentage of patients requiring systemic corticosteroid rescue for asthma during the 52-week treatment period.
- Number of hospitalizations (severe exacerbation).
- Percentage of days and episodes of > 3 days with use of PRN salbutamol rescue medication during 52-week treatment period (non-severe exacerbation).
- Percentage of days without asthma symptoms assessed by TIPP diary App (PACD).
  - A day without asthma symptoms is defined as a day during which the patient experienced no asthma symptoms (daytime and overnight; question 1, 2, 5, 6, did not use rescue medication (salbutamol) (question 3 and 7), and had no asthma exacerbation/worsening requiring systemic corticosteroids, an unscheduled visit to a doctor's office, or hospital (question 11).
- Percentage of night-time awakenings due to asthma symptoms as assessed by the TIPP diary App.
- Health utilization defined as number of physician visits during treatment.
- Number of missed days in daycare.
- Number of asthma-related events defined by use of antibiotics.
- Evaluation of TRACK at V1, at V4 and at end of treatment.
- CGI-C at end of treatment.

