### Caregiver Asthma Diary—Caregiver Instructions

Try to answer all questions as best you can. It is very important that you do not skip any questions.

This diary consists of two parts - Overnight Symptoms and Daytime Symptoms.

There are 2 questions about your child's use of  $\beta$ -Agonist medication.  $\beta$ -Agonist has several different names. For your child,  $\beta$ -Agonist is called:

$\beta$ -Agonist =  
(To be filled in by your nurse/coordinator)

Question number 8 asks about treatment with a systemic steroid (such as prednisone or prednisolone). For your child, the systemic steroid is called:

Systemic steroid =  
(To be filled in by your nurse/coordinator)

The diary begins with the Overnight Symptoms (Questions #1 to #3)

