**Overnight Symptoms: Enter your answers when your child wakes up:**

These questions cover the time from when you put your child to bed for the night to the time when he/she wakes up in the morning.

For question #1 (How much did your child cough last night ....?), please try not to check the "I do not know" response unless you really were not able to hear your child coughing.

We are asking you about coughing episodes not about individual coughs. You do not need to count the number of coughs. We would like you to give us your impression of the amount of coughing that your child had during the night.

Please fill in the number of times that your child received  $\beta$ -Agonist from the time that he/she was put to bed until he/she got up in the morning. Please enter the **total** amount that your child was given during this time for each type of  $\beta$ -Agonist used (number of puffs, nebulized treatments, teaspoons or tablets). If tablets were given, record the dose in milligrams in the comments section. If no treatments were given, fill in "0" for each type of  $\beta$ -Agonist.

The diary continues with the Daytime Symptoms (Questions #4 to #10)

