7. How **much** did your child's asthma symptoms interfere with your **child's activities** today? (Your **child's activities** could include any sort of physical activity such as running, playing, jumping, sports, bike-riding, climbing etc. or school activities) (Check **one** response)

|                        |                             |                        |                            |                          |                               |
|------------------------|-----------------------------|------------------------|----------------------------|--------------------------|-------------------------------|
| Did not interfere
① | Very mildly interfered
① | Mildly interfered
② | Moderately interfered
③ | Severely interfered
④ | Very severely interfered
⑤ |
|------------------------|-----------------------------|------------------------|----------------------------|--------------------------|-------------------------------|

8. Did your child visit a doctor, **emergency room**, or **hospital** for **asthma symptoms** (other than a scheduled visit to a doctor) or was your child **treated with a systemic steroid such as prednisone or prednisolone** (by oral, intravenous, intramuscular, or rectal administration) during the **previous 24 hours**? (Check **one** response)

No ①      Yes ① → If yes, check **all** that apply:

|                       |                                |                                         |                                      |
|-----------------------|--------------------------------|-----------------------------------------|--------------------------------------|
| Visited a doctor
② | Visited an Emergency Room
③ | Admitted to the Hospital overnight
④ | Treated with a systemic steroid
⑤ |
|-----------------------|--------------------------------|-----------------------------------------|--------------------------------------|

9. How **many times** did you give your child **β-Agonist** since he (she) **awoke this morning**? (If your child did not use any β-Agonist since waking up this morning, fill in "0".)  
Number of times:

10. How **many puffs, nebulizer treatments, teaspoons or tablets** of β-Agonist did your child use since he/she **woke up this morning**? For each kind of β-Agonist used, fill in the **total number** of puffs, nebulizer treatments, teaspoons and tablets used. (If your child did not use any β-Agonist since waking up this morning, fill in "0".)  

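### The symptom-free-day definition cites diary item numbers that contradict its own wording and the diary in Appendix 15.5; two neighbouring diary endpoints also need reconciling

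*Protocol*

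**What the plan says.** The same definition appears in sections 3.4, 6.1 and 8.3. A day without asthma symptoms is one with "no asthma symptoms (daytime and overnight; question 1, 2, 5, 6, did not use rescue medication (salbutamol) (question 3 and 7"), and with no worsening that needed systemic corticosteroids, an unscheduled doctor visit "or hospital (question 11").

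Appendix 15.5 prints the diary and says it will be delivered as an app. Questions 1 to 3 are the overnight part. For the rest, the instructions say: "The diary continues with the Daytime Symptoms (Questions #4 to #10"). They also say: "Question number 8 asks about treatment with a systemic steroid".

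The PACD paragraph in section 6.2 uses the appendix numbering. It builds the daytime score from questions 4 to 7, "which are questions regarding severity of cough, wheezing, trouble breathing, and interference with activities".

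Two other secondary endpoints rest on the same diary. One is "Percentage of night-time awakenings due to asthma symptoms as assessed by the TIPP diary App". The other is worded in 8.3 as "Percentage of days and episodes of > 3 days with use of PRN salbutamol rescue medication during 52-week treatment period". The synopsis also has more than 3 days, but sections 3.4 and 6.1 have at least 3.

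**The concern.** A definition that names item numbers is an instruction to the programmer. Here the numbers point to one set of diary items and the surrounding words describe another. A programmer who follows the numbers and one who follows the words would classify some days differently, and the protocol does not say which governs.

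At stake is the percentage of days without asthma symptoms, one of the endpoints the synopsis lists as key secondary. By number, the rule reads neither daytime cough, nor daytime reliever use, nor the steroid and health-care item. These are things the definition says must be absent.

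The count of salbutamol episodes depends on which section is read. The awakenings endpoint has no visible source item in the printed form.

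**Working it through.** No arithmetic beyond counting is involved. The check sets the rule in 3.4, 6.1 and 8.3 beside the diary items in Appendix 15.5.

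| Item | What the printed diary asks | Use in the rule |
|---|---|---|
| 1 | Cough overnight | Symptom: correct |
| 2 | Times beta-agonist given overnight | Cited as symptom: wrong heading |
| 3 | Amount of beta-agonist overnight | Rescue: correct |
| 4 | Daytime cough | Not cited |
| 5 | Daytime wheezing | Symptom: correct |
| 6 | Daytime trouble breathing | Symptom: correct |
| 7 | Interference with activities ("asthma symptoms interfere with your" child's activities) | Cited as rescue: wrong heading |
| 8 | Unscheduled doctor, emergency room or hospital visit, or systemic steroid | Not cited |
| 9 | Times beta-agonist given in the day | Not cited |
| 10 | Amount of beta-agonist in the day | Not cited |
| 11 | Does not exist | Cited for steroid, visit or hospital |

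**Count.** The rule cites seven numbers. Four are right (1, 3, 5, 6), two stand under the wrong heading (2, 7) and one is absent (11): 4 + 2 + 1 = 7. Six of the seven exist, so 10 − 6 = 4 diary items never enter the rule.

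**Is the appendix misnumbered instead?** Nothing suggests so. Section 6.2 assigns 4 to 7 the same content as the appendix, and no other numbering appears in the protocol.

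**Scoring test days.** Each day is scored twice: by the cited numbers that exist (all must be zero), and by the words (items 1 to 6 and 8 to 10 must be zero, with item 7 left out because the words do not clearly cover it).

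| Positive entries on the day | By number | By words |
|---|---|---|
| Daytime cough only | symptom-free | not |
| Daytime beta-agonist only | symptom-free | not |
| Steroid or visit item only | symptom-free | not |
| All three together | symptom-free | not |
| Wheeze plus steroid | not | not |
| Activity interference only | not | symptom-free |

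Three things follow.

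- A day is wrongly counted as symptom-free only if items 1, 2, 3, 5, 6 and 7 are all zero and at least one of 4, 8, 9 and 10 is positive.
- The misplaced item 2 changes no day's score, because a positive entry disqualifies the day under either heading.
- The misplaced item 7 matters only if the sponsor does not intend activity interference to count. In that case a day with interference alone is wrongly excluded. If item 7 is meant to count, every error from coding by number raises the percentage of symptom-free days.

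**A scoring detail on item 1.** The don't-know response carries code 5, one above the code 4 for coughing almost all night. Read as a number, it would be the worst value.

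**Salbutamol episodes.** An episode of exactly 3 days is counted under 3.4 and 6.1 and dropped under 8.3 and the synopsis.

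**Awakenings.** Item 1 asks about cough. Items 2 and 3 tell the caregiver to enter zero if the child did not wake because of asthma. A zero therefore cannot separate a night without awakening from an awakening without reliever. No printed item asks about awakening itself.

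**The case against.** The strongest reply is that the sentence defines the day in words and the numbers are only cross-references. By the words, every day with daytime cough, daytime salbutamol or a steroid is excluded, so a careful programmer would reach the right result. This stands as a limit on the consequence. It does not remove the contradiction, because the numbers are the operational part of the rule and appear unchanged in three sections.

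Several stronger readings are tempting, and the protocol does not support them.

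- A reader might infer that any day with cough, salbutamol and a steroid would be scored as symptom-free. That is not so. Wheeze, trouble breathing, activity interference, night cough or night reliever use on the same day still disqualifies it.
- A reader might infer that the misclassification inflates both arms and hides a treatment difference. The protocol gives no figure for how often the four uncited items are the only positive entries, so neither the size nor any dilution can be stated.
- A reader might infer that night-time awakenings cannot be computed. That holds only for the printed form. Section 6.2 describes the electronic diary as completed in the evening for both day and previous night, while the printed form has separate morning and bedtime parts. The app may therefore differ, and its item list is not shown.

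It can also be said that section 8 leaves analysis detail to an SAP finalized before database closure and unblinding, and that corrections could be made there. That is a fair route for the repair. It does not make this an omission left to the SAP: the protocol itself states the rule and the two thresholds, and they conflict.

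**Conclusion.** The point holds as an internal contradiction in the definition of a secondary endpoint. One cited item does not exist, two are cited under the wrong heading, and four of the ten diary items are never read. Programmed by number, days whose only positive entries are daytime cough, daytime beta-agonist use, or a steroid or unscheduled visit, alone or together, would count as symptom-free against the wording. The share of such days is unknown and cannot be derived from the protocol.

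The salbutamol-episode threshold is a plain conflict between the synopsis and 8.3 on one side and 3.4 and 6.1 on the other. The source of the awakenings endpoint is an open question.

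This is a should-fix and not a must-fix. The primary endpoint, its Cox analysis and the sample size do not use the rule. If the app carries the printed items, the data needed for a correct derivation are already collected. The conclusion assumes that the deployed app keeps the numbering of Appendix 15.5, the only numbering shown.

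**What to change.** Before unblinding:

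- **Item numbers.** Restate them in 3.4, 6.1 and 8.3 against the deployed diary. On the printed diary the wording maps to items 1, 4, 5 and 6 for symptoms; 2, 3, 9 and 10 for rescue; and 8 for steroid, visit or hospital. The sponsor should state whether item 7 counts, since requiring it is a choice of definition and goes beyond reconciling the text.
- **Item 1.** State that the don't-know response is not scored as a severity value.
- **Salbutamol episodes.** Use one threshold in the synopsis, 3.4, 6.1 and 8.3.
- **Awakenings.** Confirm that the app records them, or state which collected item the endpoint is derived from.

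The cost is protocol wording and derivation code. An added app item would be needed only if awakenings are kept as worded and the app does not already record them.

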### **Telephone contacts between visits 4–7**

Telephone visits will be performed  $6 \pm 1$  weeks after V4, V5, V6. To monitor the patient's clinical status more closely between site visits 4–7, the patient's parents/guardians will be contacted by phone midway between visits (see also flow chart for scheduled phone contacts). Before the telephone contact, the TIPP Diary APP should be reviewed. During this contact, the trial staff will inquire about the compliance of study medication use, health status, AEs, concomitant diseases and treatments, concomitant therapies, and medication, and exacerbations.

In the case of a suspected worsening of patient's clinical status, the investigator should carefully assess whether further medical assessment or treatment of an asthma exacerbation is required. If any condition qualifies as an AE, all according steps have to be taken.

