| 2. During the past 4 weeks , how often did your child's breathing problems (wheezing, coughing, shortness of breath) wake him or her up at night?                                                                                                                           |                                              |                                                |                                                   |                                                      |
| Not at all
 20                                                                                                                                                                                                                                          | Once or twice
 15 | Once every week
 10 | 2 or 3 times a week
 5 | 4 or more times a week
 0 |
| 3. During the past 4 weeks , to what extent did your child's breathing problems, such as wheezing, coughing, or shortness of breath, interfere with his or her ability to play, go to school, or engage in usual activities that a child should be doing at his or her age? |                                              |                                                |                                                   |                                                      |
| Not at all
 20                                                                                                                                                                                                                                          | Slightly
 15      | Moderately
 10      | Quite a lot
 5         | Extremely
 0              |
| 4. During the past 3 months , how often did you need to treat your child's breathing problems (wheezing, coughing, shortness of breath) with quick-relief medications (albuterol, Ventolin®, Proventil®, Maxair®, ProAir®, Xopenex®, or Primatene® Mist)?                   |                                              |                                                |                                                   |                                                      |

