### Complete in the Morning

**ANSWER IN THE MORNING:** These questions cover the period of time from when your child went to bed for the night to when he/she awoke this morning.

1. How **much** did your child **cough** last night **after** your child was put to **bed for the night** until he/she awoke this morning? (*Check **one** response*)

Did not  
cough at all  
①

Coughed  
very little  
①

Coughed  
several times  
②

Coughed  
frequently  
③

Coughed almost  
all night  
④

I do not  
know  
⑤

2. How many times did you give your child  $\beta$ -Agonist since he/she went to bed last night?  
(*If your child did not wake up last night due to asthma, then you should fill in "0".*)

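### The diary printed in Appendix 15.5 cannot yield the night-time awakenings endpoint, and missed daycare days have no stated data source

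*Protocol*

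**What the plan says.** The endpoint lists in Protocol sections 3.4, 6.1 and 8.3 include "Percentage of night-time awakenings due to asthma symptoms as assessed by the TIPP diary App" and "Number of missed days in daycare". The first names its source. The second names none. The Synopsis puts both under key secondary endpoints and gives the electronic diary/PACD as the instrument for awakenings.

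On the content of the App, section 6.2 (PACD) states: "The PACD questions will be collected electronically by the TIPPDiary app". Appendix 15.5 prints that diary. Its caregiver instructions say "The diary begins with the Overnight Symptoms (Questions #1 to #3", followed by daytime questions 4 to 10. The second overnight question begins "How many times did you give your child" and concerns beta-agonist.

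On timing, section 6.2 has the diary "answered in the evening for daytime symptoms and the previous night", whereas Appendix 15.5 has the overnight part completed in the morning, when the child wakes.

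At visits, TRACK item 2 asks how often breathing problems "wake him or her up at night", over the preceding four weeks. For the telephone contacts, section 5 says that "the trial staff will inquire about the compliance of study medication use, health status, AEs, concomitant diseases and treatments", then adds therapies, medication and exacerbations.

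**The concern.** An endpoint tied to a named instrument needs an item in that instrument that records it. If no one asks each night whether the child woke, no later analysis plan can recover the answer: it can define a percentage but cannot create the data. The nearest substitute, overnight beta-agonist use, is a different outcome.

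The loss would matter to the trial's own argument. Section 1.1 singles out nocturnal events as the setting where a 24-hour bronchodilator might be of particular use in toddlers, and the awakenings endpoint is the direct nightly measure of that. For daycare absence the worry is simpler: sites following the protocol are never told to ask.

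**Working it through.** No sample-size, power or event figure enters this point. The check is an item-by-item reading.

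**Step 1. The printed diary (Appendix 15.5).**

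| Question | What the answer records | Waking | Daycare absence |
|---|---|---|---|
| 1 (overnight) | amount of cough | no | no |
| 2 (overnight) | times beta-agonist was given | no | no |
| 3 (overnight) | quantity of beta-agonist | no | no |
| 4, 5, 6 (daytime) | severity of cough, wheeze, breathing trouble | no | no |
| 7 (daytime) | interference with activities, school activities included | no | no |
| 8 (daytime) | unscheduled care or systemic steroid | no | no |
| 9, 10 (daytime) | times and quantity of beta-agonist | no | no |

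Total: 3 overnight + 7 daytime = 10 questions; 0 record waking and 0 record daycare absence.

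**Step 2. Can questions 2 and 3 stand in for waking?** Waking is mentioned only in the filling note to these two questions, which tells the caregiver to enter zero if the child did not wake because of asthma. The overnight instructions also call for zero when no treatment was given. So:

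- child slept through: 0
- child woke, no beta-agonist given: 0
- child woke, beta-agonist given: 1 or more

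The first two cases cannot be told apart. A count above zero measures night-time reliever use, and a zero says nothing definite about waking.

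**Step 3. Other instruments.**

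- TRACK item 2 asks about waking at V1, V4 and V7, as an ordinal frequency over four weeks. On treatment that is 2 × 4 = 8 weeks of recall.
- The GINA assessment (V1, V2, V4, V5, V7; Appendix 15.1) has an any/none row that merges coughing during sleep with waking.
- TRACK item 3 concerns interference with activities, including school. It does not count missed days.
- The trial schedule, the visit lists in section 5 and the telephone-contact list have no item on daycare attendance.

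**Step 4. Is the printed diary the App?** The two uses of diary question numbers in the protocol can be set against the printed form.

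| Protocol text | Numbers used | Printed diary |
|---|---|---|
| Section 6.2, daytime score | 4–7: cough, wheeze, breathing, activities | agrees |
| Symptom-free day, symptoms | 1, 2, 5, 6 | 2 is beta-agonist use |
| Symptom-free day, rescue use | 3, 7 | 7 is activity interference |
| Symptom-free day, steroids or unscheduled care | 11 | this is question 8; the form ends at 10 |

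One use fits the printed form and the other does not, so the document does not settle which version the App carries.

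**Step 5. Completion time.** Section 6.2 (evening) and Appendix 15.5 (morning) give different times for the same overnight questions.

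**The case against.** The strongest counter-argument is that the App may not be the printed form. The symptom-free-day definition implies at least 11 questions, with question 2 a symptom item, and such a version could contain a waking item. This stands as a limit: the gap is certain only for the diary as printed. It does not remove the point. If the App differs, the protocol prints the wrong instrument; if it does not, the endpoint has no source.

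Several stronger readings are tempting, and the documents do not support them:

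- A reader might infer that waking is asked nowhere. TRACK item 2 and the GINA row do ask about it. They are four-week recall and any/none items, so they do not supply a nightly percentage, but the information is not wholly absent.
- A reader might infer that daycare absence cannot be reported at all. That endpoint is not tied to the diary, and the protocol does not list every eCRF field, so an unlisted field is possible. What can be said is that no source is stated.
- A reader might infer that reliever given for night cough without waking would count as an awakening. The filling note to questions 2 and 3 directs a zero in that case.
- A reader might want the share of awakenings that reliever use would miss. The documents give no figure for how many awakenings are treated, so none is offered.
- A reader might set TRACK's 8 weeks against a diary covering all 52. The diary pauses from May to August, 4 of 12 months, so it was never going to cover the full year.

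It is also fair that night cough is still recorded by question 1, and that the main inference of the trial is untouched.

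**Conclusion.** The point holds in limited form. As printed, the instrument named for night-time awakenings has no question that records waking (0 of 10), and its overnight medication items cannot substitute because a zero has two meanings. Missed daycare days have no stated data source. These are 2 of the 12 secondary endpoints listed for all patients. A third, days without symptoms, is defined with question numbers that do not match the printed diary, and the completion time of the overnight questions is stated in two ways.

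The primary endpoint, sample size and primary analysis are unaffected. The conclusion on awakenings assumes that the App carries the printed questions, as section 6.2 and Appendix 15.5 indicate; the conflicting numbering leaves that open. The matter should be corrected, because nightly answers that were never requested are hard to recover later.

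**What to change.** 1. Compare the protocol with the diary actually built in the App, then make the endpoint definitions, question numbers, completion time of the overnight questions and Appendix 15.5 agree with it.
2. If the App has no waking item, add one morning yes/no question, kept outside the PACD score: *Did your child wake last night because of asthma?* Define the endpoint as the percentage of recorded diary nights answered yes.
3. If it is too late to add it, drop the diary-based awakenings endpoint. Report TRACK item 2 at V4 and V7 for all children as a separately named outcome, and do not pool it with nightly data. Label question 2 only as night-time reliever use.
4. Add one eCRF question at existing visits and calls, for children attending daycare: days missed because of asthma since the last contact. Otherwise delete that endpoint.

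The cost is one App item and one eCRF field, or wording changes only if the endpoints are dropped or renamed. Daycare days would rest on recall over the 6 to 10 weeks between scheduled contacts. A nightly waking item would still have no data for the May–August pause. TRACK item 2 covers only four-week windows and overlaps with the TRACK endpoint already listed.
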